#### **8.6.4.11 Modified Nail Psoriasis Severity Index**

The nNAPSI is a tool to assess nail involvement in participants with PsA with an index score ranging to 0 to 130 for all fingernails.

Three features or groups of features (pitting, onycholysis and oil-drop dyschromia and crumbling) or each fingernail will be graded on a score of 0 to 3.

The number of pits for each finger nail is scores as 0 = 0, 1-10 = 1, 11- 49 = 2 and >50 = 3.

The score percent of nail with crumbling present it scored as no crumbling = 0, 1-25% = 1, 26 – 50% = 2 and >50% = 3.

The score percent of nail with onycholysis and/or oil drop dyschromia is: none = 0, 10% = 1, 11-30% = 2, >30% = 3.

Four features (leukonychia, splinter hemorrhages, hyperkeratosis, and red spots in the lunula) will be graded as either present (1) or absent (0) in each fingernail.

The total score is calculated by summing the score for each feature and each fingernail.

The change from baseline in mNAPSI will be analyzed using the method described in 8.6.1.2 for subjects with nail psoriasis at baseline (mNAPSI > 0). Descriptive summaries by treatment group and visit will also be displayed for Part A and Part B. For Part A and B there will also be an LOCF summary of the mNAPSI to present the absolute, change from baseline and percent change from baseline by the randomized treatment arm.

#### **8.6.4.12 Functional Assessment of Chronic Illness Therapy-Fatigue (FACIT-Fatigue)**

Other secondary endpoints include:

- Change from baseline in Functional Assessment of Chronic Illness Therapy-Fatigue (FACIT-F) score

FACIT-Fatigue is a 13-item self-assessment of fatigue and the effect on daily activities and function over the previous 7 days (See [Appendix H](#)). The 13 items use a 5-point Likert-type scale (0 = “Not at all”, 1 = “A little”, 2 = “Somewhat”, 3 = “Quite a bit”, 4 = “Very much”). The FACIT-Fatigue assessment score range between 0-52 with 0 corresponding to the highest level of fatigue and 52 corresponding to the lowest level of fatigue. The scores for the 11 items where a higher score indicates more fatigue are reversed (4-score) before being summed together with the other 2 items to give the total. If any items are missed, then the total score is adjusted by multiplying by 13 and dividing by the number of items answered.

The FACIT-Fatigue will be self-administered by the participant at Baseline, Week 4, Week 12, Week 16 and Week 20.

The exploratory null hypotheses to be tested are that the mean change from baseline over time are not different for the comparisons of interest. To test these hypotheses, a MMRM will be used including the Part A visits as detailed in section 8.6.1.2

Descriptive summaries by treatment group and visit will also be displayed for Part A and Part B.

#### **8.6.4.13 Short Form-36 Health Survey Version 2**

Other secondary endpoints include:

- Short-Form-36 Health Survey Questionnaire-Version 2 (SF-36v2) Mental Component Summary (MCS);
- SF-36v2 Physical Component Summary (PCS);

The SF36v2 is a 36-item generic HRQoL instrument that uses a recall period of 4 weeks.

Each item on the survey is answered by subjects on scales of 1 to 2, 1 to 3, 1 to 5 or 1 to 6. Some of the answers are recoded that that across all questions, a higher score indicates a better health state.

Questions 2, 3A-3J, 4A-4D, 5A-5C, 9B, 9C, 9F, 9G, 9I, 10, 11A and 11C are scored as recorded. The other questions are transformed as shown in the table below:

| Question | Original Code and re-code response |
|----------|------------------------------------|
|----------|------------------------------------|

|                                   |   |      |     |      |     |     |
|-----------------------------------|---|------|-----|------|-----|-----|
| 1 Original                        | 1 | 2    | 3   | 4    | 5   |     |
| 1 Recoded                         | 5 | 4.4  | 3.4 | 2    | 1   |     |
| 6, 11B, 11D Original              | 1 | 2    | 3   | 4    | 5   |     |
| 6, 11B, 11D Recoded               | 5 | 4    | 3   | 2    | 1   |     |
| 7 Original                        | 1 | 2    | 3   | 4    | 5   | 6   |
| 7 Recoded                         | 6 | 5.4  | 4.2 | 3.1  | 2.2 | 1   |
| 8 (if 7 is answered) original     | 1 | 1    | 2   | 3    | 4   | 5   |
| Original Response to 7            | 1 | 2-6  | 1-6 | 1-6  | 1-6 | 1-6 |
| Recoded Response                  | 6 | 5    | 4   | 3    | 2   | 1   |
| 8 (if 7 is not answered) original | 1 | 2    | 3   | 4    | 5   |     |
| 8 Recoded                         | 6 | 4.75 | 3.5 | 2.25 | 1   |     |
| 9A, 9D, 9E, 9H Original           | 1 | 2    | 3   | 4    | 5   |     |
| 9A, 9D, 9E, 9H Recoded            | 5 | 4    | 3   | 2    | 1   |     |

The raw score of each of the 8 scales is calculated by summing the re-coded scores for its relevant questions. If <50% of questions within a scale are answered then the raw score is not calculated. If more than 50% of questions are answered but <100% then take the recoded values and sum them. Then the average score is calculated for the non-missing scores and the average scored is used for the value of the missing questions.

Physical Functioning: 3A to 3J

Role limitations due to physical health (RP): 4A to 4D

Bodily pain: 7, 8

General Health: 1, 11A to 11D

Vitality: 9A, 9E, 9G, 9I

Social Functioning: 6, 10

Role limitation due to emotional problems (RE): 5A to 5C

Mental health: 9B, 9C, 9D, 9F, 9H.

Once the raw score is calculated, then it is converted to a normalized score (on a scale of 0 to 100) using the following transformation:

$$(\text{raw score} - \text{lowest possible raw score}) / \text{possible raw score range} \times 100.$$

The normalized scale score is then standardized using the following formula:

$$(\text{Normalized score} - A) / B.$$

The lowest possible raw score, possible raw score range, A and B for each scale are shown in the table below:

| Scale                                     | Lowest Possible Raw Score | Possible Raw Score Range | A        | B        |
|-------------------------------------------|---------------------------|--------------------------|----------|----------|
| Physical Functioning                      | 10                        | 20                       | 83.29094 | 23.75883 |
| Limitation due to Physical health (RP)    | 4                         | 16                       | 82.50964 | 25.52028 |
| Bodily Pain                               | 2                         | 10                       | 71.32527 | 23.66224 |
| General health                            | 5                         | 20                       | 70.84570 | 20.97821 |
| Vitality                                  | 4                         | 16                       | 58.31411 | 20.01923 |
| Social Functioning                        | 2                         | 8                        | 84.30250 | 22.91921 |
| Limitation due to emotional problems (RE) | 3                         | 12                       | 87.39733 | 21.43778 |
| Mental health                             | 5                         | 20                       | 74.98685 | 17.75604 |

The physical and mental component raw scores are then calculated based on multiplying each standardized scale score by a constant, and then adding the 8 scales together. The constants to use for the two component scores are shown below:

| Score                                     | Physical health component | Mental health Component |
|-------------------------------------------|---------------------------|-------------------------|
| Physical Functioning                      | 0.42402                   | -0.22999                |
| Limitation due to Physical health (RP)    | 0.35119                   | -0.12329                |
| Bodily Pain                               | 0.31754                   | -0.09731                |
| General health                            | 0.24954                   | -0.01571                |
| Vitality                                  | 0.02877                   | 0.23534                 |
| Social Functioning                        | -0.00753                  | 0.26876                 |
| Limitation due to emotional problems (RE) | -0.19206                  | 0.43407                 |
| Mental health                             | -0.22069                  | 0.48581                 |

The physical and mental component norm based scores is calculated by multiplying the component raw scores by 100 and adding 50.

The change from baseline in the mental component summary (MCS) and physical component summary (PCS) will be analyzed using the method described in 8.6.1.2. Descriptive summaries by treatment group and visit will also be displayed for Part A and Part B.

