#### **11.2.2.5 Short-Form-36 Health Survey-Version 2**

The SF-36v2 [Ware J. et al., 1993] will be self-administered by the participant at visits as indicated in the SOA in Section 3, Table 1.

The SF-36v2 is a 36 item generic HRQoL instrument that uses a recall period of 4 weeks. Items are grouped into 8 domains as follows:

1. Limitations in physical activities because of health problems;
2. Limitations in social activities because of physical or emotional problems;
3. Limitations in usual role activities because of physical health problems;
4. Bodily pain;
5. General mental health (psychological distress and well-being);
6. Limitations in usual role activities because of emotional problems;
7. Vitality (energy and fatigue);
8. General health perceptions.

Each question has 5 answers scored 1 (unable to) to 5 (no difficulty). The scale score of each domain is calculated based on the summed score across items included in the domain and is rescaled to 0 to 100. Version 2 of the SF-36 questionnaire will be used in the study.

In addition to domain scores, the PCS and MCS scores are calculated from the 8 domains. Component scores appreciate the impact of each domain on physical and mental health status [Maruish M.E., 2011]. Each of the 8 domain scores and the component summary scores range from 0 to 100, with a higher score indicating a better health status. The 2 component summary scores are standardized with a mean of 50 and standard deviation (SD) of 10 in the general US population. Component summary scores for a study timepoint are to be calculated from the domains completed at that same timepoint.

The SF-36v2 PCS combines 4 scales: limitations on physical activities because of health problems, limitations in usual role activities because of physical health problems, bodily pain, and general health perceptions.

The SF-36v2 MCS combines the remaining 4 scales: limitations in social activities because of physical or emotional problems, general mental health (psychological distress and well-being), limitations in usual role activities because of emotional problems, and vitality (energy and fatigue).

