#### Indices

LEI [Healy P.J. et al., 2008] is a validated enthesitis index that uses 6 sites for evaluation of enthesitis (lateral epicondyle humerus [R/L], Achilles tendon insertion [R/L], and medial condyle femur [R/L]), giving an overall score range of 0 to 6. The LEI demonstrated substantial to excellent agreement with other scores in the indication of PsA.

The SPARCC Index [Maksymowych W.P. et al., 2009] uses 18 sites: greater trochanter (R/L), quadriceps tendon insertion into the patella (R/L), patellar ligament insertion into the patella or tibial tuberosity (R/L), achilles tendon insertion (R/L), plantar fascia insertion (R/L), medial epicondyle (R/L), lateral epicondyle (R/L) and supraspinatus insertion into greater tuberosity of humerus (R/L). The maximum score is 16 (distal patella and tibial tuberosity considered as one site). The SPARCC Index has demonstrated consistent ability to discriminate between treatment and placebo in clinical studies of PsA.

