#### **8.6.4.6 Leeds Enthesitis Index (LEI) and Spondyloarthritis Research Consortium of Canada Enthesitis Index (SPARCC)**

The LEI is a validated enthesitis index which uses 6 sites for evaluation of enthesitis (lateral epicondyle humerus [R/L], Achilles tendon insertion [R/L] and medial condyle femur [R/L] giving an overall score range of 0 to 6 (see [Appendix E](#)).

The proportion of subjects with enthesitis resolution, defined as LEI = 0 will be tested using pairwise stratified logistic regression as detailed in section 8.6.1.1 in the subgroup of subjects with LEI>0 at baseline. .

The change from baseline in LEI will be analyzed using the method described in 8.6.1.2, including only subjects with LEI > 0 at baseline. Descriptive summaries by treatment group and visit will also be displayed for Part A and Part B.

The SPARCC Index uses 18 sites, greater trochanter (R/L), quadriceps tendon insertion into the patella (R/L), patellar ligament insertion into the patella or tibial tuberosity (R/L), achilles tendon insertion (R/L), plantar fascia insertion (R/L), medial epicondyle (R/L) and supraspinatus insertion into greater tuberosity of humerus (R/L). The maximum score is 16.

The change from baseline in SPARCC will be analyzed using the method described in 8.6.1.2, including subjects with SPARCC > 0 at baseline. Descriptive summaries by treatment group and visit will also be displayed for Part A and Part B. For Part A and B there will also be an LOCF summary of the LEI and SPARCC to present the absolute, change from baseline and percent change from baseline by the randomized treatment arm.

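### Two SAP scoring rules for non-confirmatory secondary endpoints are wrong as written: the SF-36 component scores use a multiplier of 100 where the protocol's scale needs 10, and the SPARCC site list omits the lateral epicondyles

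*Combined protocol and SAP*

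**What the plan says.** **SF-36.** SAP 8.6.4.13 builds PCS and MCS in four steps. Each scale's raw score is rescaled to 0–100. "The normalized scale score is then standardized using the following formula": subtract a constant A and divide by a constant B (for Physical Functioning, "83.29094 | 23.75883"). The eight results are multiplied by component constants and added. The final scores are then "calculated by multiplying the component raw scores by 100 and adding 50".

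Protocol 11.2.2.5 describes the same scores as follows: "The 2 component summary scores are standardized with a mean of 50 and standard deviation (SD) of 10 in the general US population". It also says that domain and component scores "range from 0 to 100, with a higher score indicating a better health status".

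**SPARCC.** SAP 8.6.4.6 says that the index uses 18 sites, and its list ends: "plantar fascia insertion (R/L), medial epicondyle (R/L) and supraspinatus insertion into greater tuberosity of humerus (R/L). The maximum score is 16". The corresponding stretch of the protocol list (11.2.3.6, Indices) reads "medial epicondyle (R/L), lateral epicondyle (R/L) and supraspinatus insertion into greater tuberosity of humerus (R/L"). The protocol also gives a maximum of 16, and explains that the distal patella and tibial tuberosity count as one site. The SAP does not carry that explanation over.

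SAP Section 9, which lists changes from the protocol, names one change to an instrument's scoring, BASDAI. It mentions neither SF-36 nor SPARCC.

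**The concern.** Change from baseline in PCS, MCS and SPARCC are named secondary endpoints (protocol 7.2.3, SAP 4.2). Each is analysed by MMRM, reporting least-squares means, differences and confidence intervals. Baseline PCS is also summarised (SAP 8.4.2).

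The two rules fail in different ways. The SF-36 formula puts the scores on a scale that cannot be read against the 50/10 norm the protocol promises. The SPARCC list drops two of the sites being scored. That is not a rescaling: it can change individual values, the estimates, and who is in the analysis restricted to baseline SPARCC above 0. Neither difference is declared as a change, so a programmer following the SAP has no warning.

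**Working it through.** **1. SF-36**

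Inputs: the A, B and component constants in SAP 8.6.4.13; the scale description in protocol 11.2.2.5.

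Formulas: z = (normalized score − A)/B; raw component r = Σ(constant × z); score = 50 + k × r, with k = 100 as written.

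PCS with all eight normalized scales at 50:

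| Scale | z | PCS constant | Product |
|---|---|---|---|
| Physical functioning | −1.401 | 0.42402 | −0.594 |
| Role physical | −1.274 | 0.35119 | −0.447 |
| Bodily pain | −0.901 | 0.31754 | −0.286 |
| General health | −0.994 | 0.24954 | −0.248 |
| Vitality | −0.415 | 0.02877 | −0.012 |
| Social functioning | −1.497 | −0.00753 | 0.011 |
| Role emotional | −1.744 | −0.19206 | 0.335 |
| Mental health | −1.407 | −0.22069 | 0.311 |
| **Raw component r** | | | **−0.931** (unrounded sum) |

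As written: 50 + 100 × (−0.931) = −43.1. With k = 10: 50 + 10 × (−0.931) = 40.7.

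Other profiles, computed the same way (PCS / MCS):

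| All eight scales at | k = 100 | k = 10 |
|---|---|---|
| reference mean A | 50 / 50 | 50 / 50 |
| A − B (1 SD below) | −45.1 / −45.8 | 40.5 / 40.4 |
| 0 | −226.3 / −344.4 | 22.4 / 10.6 |
| 50 | −43.1 / −85.8 | 40.7 / 36.4 |
| 100 | 140.1 / 172.8 | 59.0 / 62.3 |

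*Link between the two scales.* 50 + 100r = 10 × (50 + 10r) − 450. Any difference or change is therefore multiplied by exactly 10, and SDs and interval widths with it. A level is not. As an illustration, a 4-point treatment difference would print as 40.

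*Range.* 50 + 100r stays within 0–100 only for r between −0.5 and +0.5. On the k = 10 scale that is 45 to 55, so anyone outside 45–55 would print outside 0–100.

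*SD.* This depends on inter-scale correlations, which the documents do not give. Assuming equal correlations from 0 to 0.7, the SD of r is 0.74–0.89 (PCS) and 0.79–0.91 (MCS). The score SD is then about 74–91 with k = 100 and about 7.4–9.1 with k = 10. Nothing in that range brings k = 100 near an SD of 10.

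*P-values.* Outcome and baseline covariate both undergo the same linear transformation. MMRM estimates and standard errors both scale by 10, so test statistics are unchanged.

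**2. SPARCC**

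| Left/right pair | Protocol 11.2.3.6 | SAP 8.6.4.6 |
|---|---|---|
| Greater trochanter | yes | yes |
| Quadriceps tendon | yes | yes |
| Patellar ligament / tibial tuberosity | yes | yes |
| Achilles tendon | yes | yes |
| Plantar fascia | yes | yes |
| Medial epicondyle | yes | yes |
| Lateral epicondyle | yes | **no** |
| Supraspinatus | yes | yes |
| Points, one-site rule | 8 × 2 = 16 | 7 × 2 = 14 |
| Sites if distal patella and tibial tuberosity are split | 9 × 2 = 18 | 8 × 2 = 16 |

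The protocol list reproduces both of its stated figures, 18 sites and a maximum of 16. No single way of counting the SAP list does. The loss is 2 of 16 points (12.5% of the maximum).

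**The case against.** The strongest reply concerns consequence. These are other secondary endpoints with no confirmatory testing (protocol 12.3.3.2, SAP 8.6.4) and no place in the multiplicity procedure. A PCS of −45 would be noticed at first output and could be corrected without new data. That stands, and it sets the severity.

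A reader might infer that every PCS and MCS figure is ten times too large and outside 0–100. The arithmetic does not support this. The factor of ten applies to changes, differences, SDs and interval widths. Levels follow a different relation, agree at 50, and stay in range when the raw component is within ±0.5. The 0–100 range does not apply to changes.

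The documents do not print a multiplier of 10. It is inferred from the protocol's mean of 50 and SD of 10, given that the raw components are already in SD-type units. The inference is sound. Even with 10, one theoretical extreme falls slightly outside the range (MCS −8.8, with best physical and worst mental scores together), but this does not rescue 100.

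A reader might also infer that SPARCC results will be wrong. That is conditional on programming from the SAP list. The protocol collects lateral epicondyle tenderness, says that the enthesitis count will be used to derive both indices, and has the system perform calculations for physician assessments where required (11.2.3, 11.2.3.6). SAP 8.6.4.6 itself names the lateral epicondyle for the LEI. This looks like a copying omission, but the SAP is the stated source for derivations, and under its Section 1 departures from it must be described and justified in the clinical study report.

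Finally, the 14-point maximum relies on the protocol's one-site rule, which the SAP does not repeat. Splitting the patellar site would bring the SAP list to 16, but this contradicts the protocol and still falls short of the SAP's own 18 sites.

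**Conclusion.** Both rules are wrong as written and should be corrected; neither threatens the trial's main conclusions. The SF-36 error is definite: PCS and MCS effects and their spread are inflated tenfold, levels are distorted away from 50, and p-values are unchanged. It rests on the SAP's printed constants and the protocol's 50/10 scale; the absolute SDs quoted above also rest on assumed correlations.

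The SPARCC omission is definite in the text and conditional in effect. If the list is programmed, anyone with a tender lateral epicondyle is under-scored by up to two points, and anyone whose only tender SPARCC site is there at baseline leaves the SPARCC-above-0 analysis. How many participants that would affect cannot be told from the documents.

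The primary endpoint, key secondary endpoints, sample size and type I error control are untouched. This is a should-fix SAP correction.

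**What to change.** - **SAP 8.6.4.13:** state that the component raw scores are multiplied by 10 before 50 is added.
- **SAP 8.6.4.6:** insert the lateral epicondyle (R/L) in the SPARCC list, and add the protocol 11.2.3.6 clause that distal patella and tibial tuberosity are considered as one site. Without that clause, 18 sites and a maximum of 16 still do not agree.
- **Programs:** check PCS and MCS against a hand-scored record, for example all scales at 50 giving PCS 40.7 and MCS 36.4. Confirm that SPARCC reaches 16 when every listed site is tender.

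The cost is two short text edits and one program check. Lateral epicondyle tenderness is already in the examination list in protocol 11.2.3.6, and the SF-36 change affects only the last scoring step, so no new data are needed.

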### 8.6.4.15 ACR and PASI Composite Endpoints

4 composite endpoints will be created combining ACR and PASI endpoints:

- ACR50 and PASI90
- ACR50 and PASI100
- ACR70 and PASI90
- ACR70 and PASI100.

A subject is considered a responder for the composite endpoints at a particular timepoint if they are a responder for both of the relevant endpoints at that same timepoint. If either is missing or non-responder then the subject will be considered a non-responder.

To test these hypotheses, a pairwise stratified logistic regression will be used as detailed in [Section 8.6.1.1](#). Descriptive summaries by treatment group and visit will also be displayed for Part A and Part B combined for NRI/LOCF.

